#### **Developing a medical treatment for preeclampsia**

Historically, the development of a therapeutic treatment for preeclampsia has perhaps been hampered by a lack of understanding of the disease pathophysiology. Excitingly, within the last 12 years, our field has begun to unravel this mystery with the discovery of two placentally-derived proteins - *Soluble FMS-Like Tyrosine Kinase 1* (sFlt-1)(9-11) and *Soluble Endoglin* (sENG)(12). These are thought to play a central role in the development of preeclampsia. Their secretion by the placenta is upregulated by hypoxia, inflammation and oxidative stress. Upon entering the maternal circulation, they cause widespread endothelial and blood vessel dysfunction, culminating in maternal multisystem organ injury(4). Therefore, a safe medical treatment that reduces the placental secretion of sFlt-1 and sENG while also improving endothelial dysfunction may be a therapeutic strategy to stabilise preeclampsia.

### **1.2 RATIONALE FOR THE STUDY**

## Potential new medical therapeutic option for preeclampsia – sulfasalazine

Sulfasalazine is an anti-inflammatory medication with antioxidant properties that is currently indicated for use in the treatment of inflammatory bowel disease and rheumatoid arthritis. Importantly, sulfasalazine therapy is able to be safely continued throughout a pregnancy (classified as a 'category A' drug) (13). Given sulfasalazine's acceptability as a therapy during pregnancy, coupled with its known anti-inflammatory and anti-oxidant properties, we examined whether it might mitigate key features of the preeclampsia disease process *in vitro*.

We have demonstrated that sulfasalazine reduces sFlt-1 and sENG secretion from human placenta, including from placental samples obtained from patients diagnosed with preterm preeclampsia (Figure 1A). Importantly, we have also shown that it can significantly improve vascular function by quenching markers of endothelial dysfunction (Figure 1B) and induce whole blood vessel dilation.

[figure not shown]

**Figure 1:** Sulfasalazine reduces A) sFlt-1 secretion from preeclamptic placenta and B) a marker of endothelial dysfunction VCAM-1 induced in endothelial cells with the addition of preeclamptic serum.

Given the promising *in vitro* data and sulfasalazine's established safety profile in pregnancy, we now wish to progress this concept to the clinic. We hope to recruit 20 participants with preterm preeclampsia and treat them with 3 g of oral sulfasalazine per day. The primary aims of this study are to:

- Assess the pharmacokinetic profile of sulfasalazine administered to pregnant women with preterm preeclampsia
- Gain further information on the safety profile of sulfasalazine therapy administered to women with preterm preeclampsia

Secondly, we will assess key clinical and biochemical features of preterm preeclampsia in women taking sulfasalazine. If effective, this will provide the first evidence that sulfasalazine may be a treatment for preeclampsia in humans. It will form the basis for a larger randomized controlled clinical trial aiming to establish sulfasalazine as a medical treatment for preeclampsia.

### 1.3 POTENTIAL RISKS TO PARTICIPANTS

We expect the proposed treatment will be safe and well tolerated. Sulfasalazine is classified as a 'category A' drug in pregnancy - it has historically been taken by large numbers of pregnant and child-bearing-aged women; and is not known to cause any increase in the frequency of direct harm, indirect harm, or anomalies in the developing fetus in either humans or animals (13). Importantly,

sulfasalazine therapy is currently continued as a treatment option for pregnant women who have concomitant rheumatoid arthritis or inflammatory bowel disease.

Possible fetal risks:

Not known to cause anomalies in/harm to the developing fetus (13).

Possible maternal risks:

Patients with preterm preeclampsia may experience discomforts or inconveniences relating to their admission to hospital, clinical examinations and blood tests, regardless of whether or not they decide to participate in the study. However, patients recruited to the study would undergo additional examinations and pathology tests that are supplementary to their routine clinical care, and as such, may experience an increase in these discomforts and inconveniences. These additional study requirements will be outlined in detail to all potential participants during the informed consent process.

Sulfasalazine is generally well-tolerated. Side effects relating to the medication can be either dose-related or idiosyncratic.

Dose-related side effects include gastrointestinal side effects (nausea, vomiting and diarrhoea), central nervous system (headache) and hematologic toxicities (including leukopenia, haemolytic anaemia and megaloblastic anaemia). Dose-related symptoms are generally experienced when taking sulfasalazine in larger doses (>4 grams per day) than we propose to administer in this study. Our participants will receive a maximum daily dose of 3 grams of sulfasalazine and will be monitored for dose-related side effects every 1-3 days by a member of the research team.

Idiosyncratic side effects of sulfasalazine are rare. They generally occur in the first 3 months of treatment, and symptoms may include skin rash, hepatitis, pancreatitis, pneumonitis, agranulocytosis and aplastic anaemia. These effects are usually dose-dependent. They are rarely seen in patients on low dose sulfasalazine, similar to the levels we propose to use for this study. Importantly, these side effects are generally transient and recovery is usually seen 1-2 weeks after ceasing the medication. Study participants will be monitored for the occurrence of idiosyncratic side effects in relation to taking sulfasalazine. However, as our study population will be made up of young, generally healthy women and we propose to use low doses of sulfasalazine therapy for a few weeks at most, we believe they would be at very low risk of developing these complications in relation to this study.

## **1.4 POTENTIAL BENEFITS**

### **1.4.1 Safe treatment for mothers; better outcomes for babies and families**

There are some potential benefits for participants related to their participation in the study. By offering a possible medical treatment for preeclampsia, we hope to quench the disease process using a well-tolerated medication with an established low-risk harm profile. Potential maternal benefits include disease stabilisation and a reduction in multisystem organ involvement (including

vessel; hepatic; renal; blood; and neurological disease), injury and failure. This could allow for the safe prolongation of some pregnancies to more advanced gestations. This would reduce premature delivery and the associated complications which include cerebral palsy, respiratory distress syndrome, chronic lung disease, retinopathy of prematurity, necrotising enterocolitis and other common morbidities of the preterm or growth-restricted neonate. Broadly, this treatment has the potential to reduce the short- and long-term social, practical, emotional and financial strains placed on women and families who experience preterm preeclampsia.

#### **1.4.2 Cost benefits**

Preeclampsia has an estimated global economic cost of USD\$3 billion annually (14), with the impact borne by individuals, families, businesses, and health and welfare systems. Given that women are hospitalised with preeclampsia will be unable to perform their normal paid and unpaid occupations and carer responsibilities for a time, there can be a significant loss in productivity associated with the disease. A loss in household earning capacity (which often subsequently leads to an increase in reliance on government support) can remain throughout parents' working lives if they have a baby born with severe long-term sequelae, as well as possibly impacting on the child's ability to work and live independently once they reach adulthood.

There can be large healthcare costs associated with the inpatient treatment of women who develop preterm preeclampsia – this strain on the health care system can become even more substantial if the pregnancies result in the premature births of babies who then require a significant period of intensive hospitalisation or have long-term, complex health care needs. A medical treatment for preeclampsia could reduce this financial and social burden by reducing iatrogenic prematurity resulting in improved long-term health of the child.

#### **1.4.3 Reduction of maternal and fetal mortality in developing countries**

Although the burden of disease and economic costs associated with preeclampsia is significant in Australia, it is dwarfed by the impact endured by developing countries. Along with sepsis and haemorrhage, preeclampsia is one of the leading global causes of maternal and infant mortality, particularly in low-income settings (15). It is estimated that:

- There are approximately 830 maternal deaths globally every day from preventable causes in pregnancy and childbirth
- Approximately 99% of maternal deaths occur in developing countries
- Up to 25% of maternal deaths in some global regions are directly attributable to hypertensive disorders of pregnancy
- There are far greater numbers of fetal and neonatal deaths resulting from preeclampsia. (16, 17)

It is an important aspect of publically-funded research for the investigators to consider how any positive findings might be equitably translated for use into different health care contexts, such as in

rural and remote communities, developing countries and other resource-poor settings. Sulfasalazine is a medication already known to have a low-risk harm profile in pregnancy; is generally well-tolerated; is inexpensive; readily available; and vitally, for resource-poor or remote settings, does not require refrigeration to maintain its molecular stability. If sulfasalazine can be established as a safe and effective treatment for preeclampsia, it could be realistically translated into use in isolated communities within Australia, as well as being potentially appropriate for use in developing countries. This could potentially trigger an exponential improvement in the current global perinatal mortality figures, which are particularly poor in isolated communities and developing countries.

## **2 STUDY OBJECTIVES**

An early (phase II) clinical trial assessing the safety and pharmacokinetic profile of sulfasalazine in patients with preeclampsia is required to assess the suitability of sulfasalazine as a potential medical treatment for preeclampsia.

### **2.1 OBJECTIVES**

#### **2.1.1 Primary objectives**

The primary objective of this study is to establish the safety and pharmacokinetic profile of sulfasalazine in patients with preterm preeclampsia. In particular, we will be examining:

- Any adverse effects in the treated mother (safety data)
- Fetal/neonatal mortality and morbidity outcomes of participants' babies; including neurological, respiratory, eye and gastrointestinal disease (safety data)
- Maternal plasma and urine levels of circulating and excreted sulfasalazine following dose administration (pharmacokinetic data)
- Maternal blood, cord blood and placental levels of sulfasalazine following delivery (pharmacokinetic data)

#### **2.1.2 Secondary objectives**

To determine the effects of sulfasalazine on the clinical outcomes and biochemical markers of preeclampsia disease progression in preterm pregnancies by assessing for:

- Length of gestation prolongation (when compared with a contemporaneous cohort)
- Occurrence of clinical symptoms of preeclampsia
- Biochemical markers of preeclampsia disease; including but not limited to full blood count, Liver Function Tests (LFTs), renal function, proteinuria and haematological parameters
- Serum biomarkers of preeclampsia including but not limited to sFlt-1, sENG, Placental growth factor, endothelin 1, cellular adhesion molecules and cytokines.

## **2.2 ENDPOINTS**

### **2.2.1 Primary endpoint**

Delivery of the pregnancy.

### **2.2.2 Secondary endpoints**

#### Laboratory endpoints/measures of interest:

- Serum biomarkers of preeclampsia (sFlt-1, sENG, placental growth factor, V-CAM, I-CAM and Endothelin; and 10 cytokine bioplex assay) during disease progression
- Biochemical markers of preeclampsia during disease progression

#### Clinical endpoints/measures of interest:

- Adverse Events (AEs) in mother and/or baby
- Time (days) to delivery of pregnancy after initial sulfasalazine dose
- Change in maternal systolic and diastolic blood pressure (mmHg)
- Change in maternal proteinuria (g/mmol)
- Emergence of/change in other clinical symptoms of preeclampsia
- Maternal development of Haemolysis/Elevated Liver enzymes/Low Platelets (HELLP) syndrome
- Neonatal morbidity/mortality outcomes
- Acceptability of treatment and side effects to participants

## **3 STUDY DESIGN**

This study is an early (phase II), unblinded, single-arm, proof of concept clinical intervention trial aiming to assess the safety and pharmacokinetic profile of sulfasalazine as a treatment for preterm preeclampsia.

20 participants with singleton pregnancies between 30+0 and 36+0 weeks gestation will be recruited over a two year period. Recruitment will occur at the Mercy Hospital for Women (15 participants) and Sunshine Hospital (5 participants) following a patient's antenatal admission to hospital with a diagnosis of proteinuric preeclampsia, as per the Society for the Study of Hypertension in pregnancy guidelines(1).

All recruited participants will receive 3 grams of sulfasalazine upon enrolment in the study. The following pathology tests will be collected in relation to the study:

Once the participant has been taking sulfasalazine for >30 hours:

- 6 x blood samples ( $\geq 5$  ml per sample collected in pink-topped plasma EDTA tubes) to assess maternal plasma levels and pharmacokinetics of sulfasalazine will be collected from the patient's dedicated intravenous cannula during one 12 hour period
- 3 x Mid-stream urine (MSU) samples ( $\geq 5$  ml per sample) to assess for maternal sulfasalazine excretion will be collected in one 12 hour period.

During remainder of pregnancy:

- When blood tests are collected as part of clinical care, an additional sample ( $\geq 5$  ml per sample collected in pink-topped plasma EDTA tube) will be collected to assess maternal serum biomarkers of preeclampsia including:
  - Anti-angiogenic factors associated with preeclampsia (sFlt-1 and sENG)
  - Biomarkers of endothelial injury (V-CAM, I-CAM and Endothelin)
  - 10 cytokine bioplex assay

Postnatally:

- Maternal blood (1 x pink-topped plasma EDTA tube), umbilical cord blood (1 x pink-topped plasma EDTA tube) and placental samples (6 x 30 g tissue samples) will be collected at delivery to assess for circulating sulfasalazine levels in both mother and baby

The hospitals' local Standard Operating Procedures (SOP) of managing preterm preeclampsia (including blood tests  $\geq 3$  times per week; twice weekly growth and wellbeing ultrasounds; *umbilical artery (UA) Doppler* and CTG monitoring 3 times per week) - or management as otherwise ordered by the treating obstetric unit – will be followed.

Participants will be visited every 1-3 days from recruitment until delivery (while they remain inpatients) by a member of the research team to monitor for AEs or possible side effects of sulfasalazine, and to ensure the participant's ongoing willingness to participate in the trial. Participants who are discharged home prior to the birth of their baby will be reviewed by a researcher each time they attend their hospital for an outpatient review until they are readmitted or their baby is born. A member of the research team will be on call to attend or for advice relating to concerns raised by the participants or the clinicians providing their direct care.

Biochemical markers of preeclampsia disease (such as LFTs and proteinuria) will be monitored as a part of standard clinical care. The researchers will also have access to these routine pathology results – this data forms some of the secondary outcomes of the study.

The timing of delivery and any deviations from routine clinical care will be determined by the treating clinician or obstetric unit – not by a member of the research team. In the case where a member of the research team is also acting as the treating clinician, these decisions will be made in consultation with other members of the treating obstetric unit, with the best interests of mother and baby as the paramount consideration.

The medical histories of babies born to participants (including any pathology results from tests ordered by the treating clinicians) will be reviewed postnatally to assess for neonatal outcomes and AEs. A 'closing out' visit on the postnatal ward (or phone call following maternal discharge) will be made following the delivery of each participant's baby.

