## **7 STUDY ASSESSMENTS**

### **STUDY ASSESSMENTS PRIOR TO TREATMENT**

As part of routine clinical care, examinations and pathology tests will have been carried out prior to a participant's screening for recruitment. The results of these tests and examinations help to establish a patient's suitability for the study and give additional details that may be pertinent to the study analysis for stratification purposes. The following test and examination results will be transcribed as appropriate into the *Case Report Form* (CRF), following a participant consenting for inclusion in the study:

- Gravida and parity
- Estimated due date
- Height, weight and BMI at booking and at recruitment
- Blood pressure readings throughout pregnancy
- Medical progress notes tracking the history of the evolution of preeclampsia
- Pathology tests (including but not limited to *Full Blood Examination* (FBE); *Urea and Electrolytes* (U&Es); LFTs; Uric Acid; Oral Glucose Tolerance Test; coagulation profile; UA Dopplers; growth and wellbeing ultrasounds; etc.)
- Urine spot protein/creatinine ratio; and/or 24-hour urine collection
- First and/or second trimester dating ultrasound
- Aneuploidy screening tests
- Morphology ultrasound

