#### STUDY ASSESSMENTS - AFTER 30 HOURS OF SULFASALAZINE TREATMENT

- Insertion of a dedicated intravenous cannula
- Six blood ( $\geq 5$  ml collected in pink-topped plasma EDTA tubes each time) tests over one 12 hour period (via the cannula)
- 3 x MSU samples ( $\geq 5$  ml per sample, collected in yellow-topped sterile specimen pots) over one 12 hour period
- At MHW only – Repeated brachial artery flow-mediated dilatation measurements

After these specific samples and measurements are collected, study assessments will follow the pattern of normal clinical care as per local SOP for the treatment of preeclampsia. Study-specific blood samples ( $\geq 5$  ml collected in pink-topped plasma EDTA tubes) to assess for maternal serum biomarkers of preeclampsia will be collected along with any clinically indicated blood tests, as dictated by the treating obstetric team (usually every 2-3 days).

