### 7.4 STORAGE AND ANALYSIS OF SAMPLES

The research team will organise for the collection, transport, short-term storage, processing, analysis and disposal of the following blood, urine and placental samples:

- 6 x blood samples collected during one 12 hour period  $\geq 30$  hours following the 1st dose of sulfasalazine to assess for maternal plasma levels and pharmacokinetic activity of sulfasalazine
- 3 x MSU samples collected during one 12 hour period following the commencement of sulfasalazine therapy dose to assess for maternal excretion of sulfasalazine and its metabolites
- Subsequent study blood samples collected concurrently with routine pathology to assess for maternal serum biomarkers of preeclampsia
- Maternal blood, cord blood and placental samples collected at delivery

Research samples for this study will be managed at the University of Melbourne Department of Obstetrics and Gynaecology laboratory at the Mercy Hospital for Women and the research laboratory at Sunshine Hospital. These samples will be handled and analysed by appropriately qualified members of the research team and laboratory staff in accordance with University of Melbourne laboratory SOPs. These samples will be disposed of as soon as they are processed and the required data has been extracted.

All other pathology samples will be sent for analysis to each participating site's contracted pathology provider. The research team will only access the results of these tests from patient files to be

transposed into the CRF. Responsibility for the ordering, collection, transport, analysis, storage, and disposal of these samples will remain with the clinical care team and the local pathology service providers (as appropriate).

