### **9.2 PROPOSED ANALYSES**

Statistical analysis for this study will be performed using *GraphPad Prism 6* (GraphPad Software, La Jolla, CA). Given the study design and objectives of this particular trial:

- There is no comparison arm, so clinical variables and the clinical course will be presented as descriptive statistics
- There is no power calculation to perform
- Maternal and neonatal continuous variables will be statistically analysed using a t-test (parametric) or a Mann-Whitney test (non-parametric), as appropriate
- Categorical variables will be statistically analysed using a chi-squared test or Fisher's exact test, as appropriate
- Biomarker concentrations will be assessed as continuous variables
- Steady state sulfasalazine pharmacokinetic parameters will be estimated using standard non-compartmental techniques and normalized using actual body weights
- A p value of <0.05 will be considered statistically significant.

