#### **9.2.1 Primary outcome analysis**

- The primary objective of this study is to assess the safety of administering sulfasalazine in patients with preterm preeclampsia
- We will assess for adverse effects in the mother and the fetus/neonate
- We will assess mortality and morbidity outcomes - including neurological, respiratory, eye disorders and gastrointestinal disease - in the fetus/neonate
- We will also assess the pharmacokinetic profile of sulfasalazine which will involve taking maternal serum levels of sulfasalazine following administration; maternal urinary excretion of sulfasalazine following administration; and maternal serum levels, cord blood levels and placental levels of sulfasalazine at delivery
- Pharmacokinetic parameters include maximum concentration (C-max); time to maximum concentration (T-max); area under the concentration time curve (AUC); apparent oral clearance (CL/F); half-life; and renal clearance.

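### Renal clearance is a named primary pharmacokinetic parameter, but the three mid-stream urine specimens give concentrations without volumes, so it cannot be calculated by the stated method

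*Protocol*

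**What the plan says.** Protocol section 9.2.1 (primary outcome analysis) says the pharmacokinetic assessment will include urinary excretion of sulfasalazine, and ends its parameter list with "apparent oral clearance (CL/F); half-life; and renal clearance". C-max, T-max and AUC come before these, which makes six parameters. Section 9.2 fixes the method: "Steady state sulfasalazine pharmacokinetic parameters will be estimated using standard non-compartmental techniques and normalized using actual body weights". Among the primary objectives, section 2.1.1 asks for plasma and urine levels of the drug.

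The urine sampling is described in three places:

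- Section 3 (study design): "3 x Mid-stream urine (MSU) samples" of at least 5 ml, in one 12-hour period once treatment has run for more than 30 hours.
- Section 7 (assessments after 30 hours): three specimens of at least 5 ml "per sample, collected in yellow-topped sterile specimen pots) over one 12 hour period".
- Section 7.4 (storage and analysis): "3 x MSU samples collected during one 12 hour period following the commencement of sulfasalazine therapy dose", taken "to assess for maternal excretion of sulfasalazine and its metabolites".

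Six plasma samples are drawn by cannula, also in one 12-hour period. The only complete urine collection mentioned is in the list of pre-treatment routine results in section 7: "Urine spot protein/creatinine ratio; and/or 24-hour urine collection".

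**The concern.** Renal clearance needs an amount of drug in urine, and an amount is a concentration multiplied by a volume. A mid-stream specimen is, by its nature, part of one void. The protocol asks for no complete collection, no emptying of the bladder at the start and end of the window, no record of volume voided, and no creatinine on these specimens. The numerator of a parameter promised in the primary outcome analysis would therefore not exist.

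The loss cannot be repaired at the analysis stage. Any reported value would rest on an assumed urine output, in women whose disease, according to section 1.1, can progress to renal failure. Assuming a common output would therefore be hard to defend.

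**Working it through.** The plan gives no figure for renal clearance or urine volume, so there is nothing to reproduce. The check compares what the stated method needs with what is collected.

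**Definition (standard non-compartmental):**

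CLr = Ae(0–12 h) / AUC(0–12 h), with Ae = Σ (urine concentration in interval i × total volume voided in interval i).

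**What is available:**

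| Quantity | Source in protocol | Available? |
|---|---|---|
| AUC(0–12 h) | six plasma samples in 12 h (sections 3, 7, 7.4) | yes |
| Urine concentration | three mid-stream specimens (same sections) | yes, at three times |
| Total volume voided | none | no |
| Same 12 h for urine and plasma | not stated | unclear |

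On the last row, sections 3 and 7 list both kinds of sample after 30 hours, and the notes to Table 2 agree. But section 3 gives each its own 12-hour period without saying it is one and the same. Section 7.4 ties only the blood samples to at least 30 hours after the first dose; it places the urine simply after the start of therapy. The windows probably coincide, but the text does not require it.

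**Dependence on the missing volume.** Hold the specimens and the AUC fixed, with purely illustrative values: mean urine concentration 100 mg/L and AUC(0–12 h) 100 mg·h/L. Vary only the 12-hour urine volume, also assumed:

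| Assumed volume (L) | Ae = 100 × volume (mg) | CLr = Ae / 100 (L/h) |
|---|---|---|
| 0.3 | 30 | 0.3 |
| 0.5 | 50 | 0.5 |
| 1.0 | 100 | 1.0 |
| 1.5 | 150 | 1.5 |

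The same specimens fit a range of 1.5 / 0.3 = 5-fold. With 0.4 to 1.5 L instead, the range is 1.5 / 0.4 = 3.75-fold. These ratios are simply the ratios of the assumed end points. What holds whatever range is chosen is that CLr is directly proportional to a volume nobody records.

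**Could the 24-hour urine supply it?** No. It is an optional routine test taken before treatment, when no study drug is present, and it covers a different period.

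**Could creatinine supply it?** Indirectly: CLr ≈ (urine drug / urine creatinine) × (plasma creatinine / mean plasma drug) × creatinine clearance. This needs creatinine in the same urine specimens and a creatinine clearance for the same period. Neither is specified for the pharmacokinetic window. If creatinine clearance had to be assumed, say 60 to 150 ml/min, the result would carry a 150 / 60 = 2.5-fold range.

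**The case against.** The strongest reply is that little is lost. The primary objective in section 2.1.1 asks for urine levels, and sections 3 and 7.4 say the specimens are there to assess excretion. Three concentrations do give urine levels and do show that drug and metabolites are excreted. Five of the six named parameters need no urine at all. The product information (Appendix 1, Absorption) says only a few percent of a dose leaves unmetabolised in urine. This is a descriptive study of 20 women, with no power calculation and no decision tied to renal clearance. All of that stands, and it limits the point to one parameter.

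Some stronger readings are tempting but not supported:

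- **The pharmacokinetic primary objective fails.** It does not: C-max, T-max, AUC, CL/F and half-life do not depend on urine volume, and urine levels can still be described.
- **Renal clearance could not be estimated by any means.** This is too absolute, because the creatinine route exists in principle. It would need an assay that the protocol does not specify, done before the samples are discarded under section 7.4, and it is not the method named in section 9.2.
- **The specimens are too small.** At the minimum, 3 × 5 ml = 15 ml is 1 to 5% of the assumed 0.3 to 1.5 L. That fraction does not measure the error: 5 ml is a floor, and a small aliquot is enough when the total volume is known.
- **The volume uncertainty is about as large as the 2 to 10% urinary recovery in Appendix 1.** The two are not comparable. The recovery figure is a fraction of a single dose, not a clearance and not a steady-state quantity.

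None of these limits answers the core mismatch between the parameter listed in section 9.2.1 and the specimens in sections 3, 7 and 7.4. Nor is it a detail that can be left to a statistical analysis plan, since analysis cannot recover an unmeasured volume.

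**Conclusion.** The point holds in a limited form. Followed as written, the protocol cannot deliver renal clearance by the non-compartmental method it names, because it collects urine concentrations without volumes and does not state that the urine and plasma windows coincide. One of six pharmacokinetic parameters is affected; the other five, the urine levels and the safety assessment are not.

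This conclusion rests on the definition of renal clearance and on the protocol's sampling text, not on any assumed number. The fivefold and 3.75-fold ranges are illustrations from assumed volumes and should not be quoted as the error of this trial. The change should be made because a primary-outcome parameter is promised and the loss is permanent for each woman sampled. The trial's main conclusions do not turn on it.

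**What to change.** **Preferred, if renal clearance is wanted.** In sections 3, 7 (assessments after 30 hours) and 7.4, replace the three mid-stream specimens with a complete urine collection over the same 12 hours as the plasma profile:

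- bladder emptied at the start, with that urine discarded, and again at the end, with that urine kept;
- total volume recorded, as one interval or several;
- an aliquot of at least 5 ml kept from each interval.

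One interval is enough for the amount excreted; three are optional. Add a volume field to the case report form.

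**Alternative, if it is not wanted.** Delete renal clearance from section 9.2.1 and either report urine concentrations descriptively or measure creatinine in the same urine and plasma samples before disposal and report a drug-to-creatinine clearance ratio.

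**Cost.** The first option takes an amendment to the wording, modest nursing effort and some incomplete collections. All participants begin as inpatients (section 6.4) and are cannulated for the plasma samples, so the added burden is limited. However, the optional pre-treatment 24-hour urine does not show that complete collections are routine during this window. The second option costs one reported parameter and, if the ratio is used, a creatinine assay. Either change should be made before further women are sampled.
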